#### Primary analysis

- The primary analysis population is intention-to-treat, including all randomised participants, regardless of treatment received.
- The outcome variable will be change in Total log10 CFU from baseline to assessment time point.
- The primary analysis will include all randomised participants with baseline and at least one post-baseline measure.
- The dependent variable will be total log CFU.
- The model will be a mixed effects model
- Fixed effects in the model will be:
  - Antiseptic (1% CHG, 2% CHG, OCT)
  - Frequency of application (once, multiple)
  - Time point of assessment: hour of swab (continuous; mfp will be used to assess linearity)
  - Baseline total CFU (continuous; mfp will be used to assess linearity)
- Individual will be fitted as a random effect to account for repeated measures within individuals. Goodness of fit of an unstructured covariance matrix will be assessed and used if it is clearly a better fit to the data than random intercepts only.
- Goodness of fit of an interaction between baseline total CFU and timepoint of assessment will be assessed and included in the model if clearly a better fit.
- Normally distributed errors will be fitted.
- The intercept (reference treatment category) will be once only 1% CHG as this is the lowest concentration of CHG, which is believed to be more readily available than OCT, and so would be the most straightforward to implement. The standard of care control will not be used as the reference as the sample size for this arm is lower than for the factorial arms and so power for comparisons is correspondingly lower.
- Comparison of effects between factorial arms will be assessed by testing whether the null hypothesis of no treatment effect can be rejected (equivalent to using the estimate and 95% confidence interval of the estimate of the difference to the intercept).
- Comparisons between other arms and between arms and the SOC arm may also be performed. There will be no formal correction for multiple testing but interpretation will take multiple testing into consideration.
- Model fitting will use restricted maximum likelihood (REML) and p-values are derived using the Kenward-Roger approximation.

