#### **4.10.4. Analysis plan (brief)**

The analyses will be described in detail in a full Statistical Analysis Plan. This section summarises the main issues.

The primary analysis population is intention-to-treat, including all randomised participants, regardless of treatment received. This corresponds to estimating the impact of the effectiveness of the treatments. However, in secondary analyses we will also use inverse-probability weighting methods to adjust for deviation from randomised strategy, which is a more efficient approach than defining a per-protocol population.

Analysis of the co-primary endpoints will compare within-individual differences over time across randomised arm to maximise the information gained from the trial. Analysis will use linear mixed-models, with individual as a random effect, will adjust for baseline values of each outcome, and use Normally distributed errors. Analysis will be both frequentist, enabling straightforward comparison between arms (primary analysis since sample size is based on this), and Bayesian, enabling estimation of the probability that one arm is truly superior to another. This is more powerful when sample sizes are small as use of priors provides additional information. Sensitivity analysis to prior assumptions will be performed using optimistic, non-informative and sceptical priors.

The effect of each treatment arm will be assessed within a single model with each factor being fitted independently as a factor, and not as a continuous variable. Comparison of main effects within arms will be assessed using the estimate and 95% confidence interval of the comparison of differences between factors and in comparison, to control. As this is a pilot trial, the sample size was not powered to robustly detect interactions between treatment and frequency and so we will not test these formally, but will use exploratory analyses to assess whether there is any evidence supporting individual interactions testing each one, one at a time.

Similar mixed models will be used to analyse change in skin temperature after vs before each application, including individual as a random effect, the change in temperature as the outcome and the pre-application (baseline) temperature as a factor.

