#### Neonatal strata

1. Born by planned elective caesarean section
2. Born to mothers recruited in the trial
3. Poor skin condition (skin score of 2 or more in any of three domains (see [Appendix I](#))) at the time of enrolment
4. Known congenital or acquired skin disorder or defect at time of enrolment
5. Antiseptic application or enrolment in the trial determined inappropriate in the opinion of the enrolling clinician
6. Any recent or planned (within 4 hours) iodine application to body
7. Any planned or previous lumbar puncture
8. Unable to obtain parental or guardian consent

The primary analysis population is intention-to-treat, including all randomised babies, regardless of treatment received. This corresponds to estimating the impact of the effectiveness of the treatments. However, in secondary analyses we will also use inverse-probability weighting methods to adjust for deviation from randomised strategy if non-compliance rates are >15%, which is a more efficient approach than defining a per-protocol population (1).

Loss-to-follow rates are unknown but may be high as participants may give birth (in the maternal strata) or be discharged (in the neonatal strata) before all planned swabs are taken. Missing swabs

will be monitored and participants without baseline and two post-baseline swabs may be replaced to maintain power. However, all baseline and post-baseline results will be included in analyses.

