## **2.6. Estimands**

The intervention is the randomised antiseptic and frequency of application.

The patient population is labouring mothers and new-born babies, with birth weight over 1kg admitted to hospital, as defined by the inclusion and exclusion criteria.

The co-primary endpoints are change in skin bacterial colony load, taken from vaginal and perineal swabs in the maternal strata and neck and perirectal swabs in the neonatal strata.

The population-level summary which provides a basis for comparison between treatment conditions is the difference in mean log colony forming units adjusted for baseline value.

Anticipated intercurrent events and associated strategy are:

- Loss to follow-up: rates are unknown but may be high as not many women are anticipated to labour for 32h. The mixed model gives valid estimates assuming outcomes are missing at random.
- Deviation from randomised strategy (antiseptic application and frequency as per protocol) will be assessed using multiple sensitivity analyses:
  - sensitivity analysis will censor at deviation from randomised strategy. Estimated treatment effects will then correspond to the (hypothetical) setting of no deviation.
  - sensitivity analysis using (a) post-intercurrent event data where appropriate and (b) MI will be used to assess robustness of treatment effect inferences where rates of deviation from protocol are above 15%.
  - sensitivity analysis using Inverse-probability weighting methods to adjust for deviation from randomised strategy if deviation rates are above 15%.

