**Deviation from randomised strategy multiple imputation analysis**

- The primary efficacy analysis described above will be repeated using multiple imputation on individuals censored at the point of deviation from randomised strategy if deviation rates are above 15%.

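### The primary analysis is labelled intention-to-treat but excludes participants without a baseline result, whose later swabs could be kept at almost no cost

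*Protocol*

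**What the plan says.** Protocol section 4.10.4 sets the population: "The primary analysis population is intention-to-treat, including all randomised participants, regardless of treatment received". SAP section 4.6 (Primary analysis) repeats this, and two bullets later restricts the model: "The primary analysis will include all randomised participants with baseline and at least one post-baseline measure".

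SAP section 1.2 allows replacement of participants who lack a baseline swab and two later swabs, and continues: "However, all baseline and post-baseline results will be included in analyses". SAP section 3.3 repeats that sentence, again straight after a replacement rule.

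SAP section 4.6 describes the outcome twice. One bullet reads "The outcome variable will be change in Total log 10 CFU from baseline to assessment time point", another "The dependent variable will be total log CFU". Baseline also enters the model as a fixed effect: "Baseline total CFU (continuous; mfp will be used to assess linearity)".

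On missing data, SAP section 2.6 says "The mixed model gives valid estimates assuming outcomes are missing at random". Multiple imputation appears only for departures from the allocated strategy; the primary analysis is then "repeated using multiple imputation on individuals censored at the point of deviation from randomised strategy if deviation rates are above 15"%. Inverse-probability weighting has the same purpose.

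**The concern.** Someone with post-baseline swabs but no baseline total is inside the population as labelled, inside the statement that all results are used, and outside the model. An analyst cannot satisfy all three.

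Such cases are possible. The total is the sum of two site-specific log counts (SAP section 2.1), and no rule is given for a total with one site missing, so losing either baseline swab would appear to leave the total undefined. Swabs travel by courier to a laboratory in another city (protocol section 4.7.2). SAP section 4.5 plans to report how many participants had a baseline swab.

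Nothing in the plan brings these participants back. The missing-at-random statement concerns outcomes, while a missing covariate removes the whole record. Imputation and weighting are reserved for departures from strategy. Replacement adds a new participant but not the excluded one's swabs. At stake are an accurate description of the primary population and some precision in a trial of 21 per group whose sample size text states no allowance for loss.

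**Working it through.** **1. The statements side by side, by type of participant**

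| Participant | All randomised (4.6, first bullet) | All results used (1.2, 3.3) | Admitted by 4.6 rule |
|---|---|---|---|
| Baseline and later swab | yes | yes | yes |
| Later swab, no baseline total | yes | yes | no |
| Baseline only | yes | yes | no |

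The second row is the avoidable loss. The third row also contradicts the label, but a baseline-only participant adds almost nothing to a baseline-adjusted comparison.

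**2. Is a baseline needed?** If the outcome is change, yes: without a baseline there is no outcome. If the dependent variable is total log CFU, no. For participants with both values, and with baseline entered linearly, regressing change or total on treatment and baseline gives the same treatment coefficients. Choosing total log CFU therefore costs nothing for complete participants. The baseline swab precedes antiseptic, so randomisation makes baseline independent of arm, and filling in a value that ignores arm does not favour any arm.

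**3. The plan's own power figure.** Inputs (protocol section 4.5, SAP section 2.4): 42 per antiseptic (2 × 21), difference 0.82 SD, two-sided alpha 0.012, critical value 2.512.

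Power = Φ(0.82 × √(n/2) − 2.512). With n = 42: 0.82 × √21 = 3.758, and Φ(1.246) = 0.894. The stated 90% is reproduced to within a point. A noncentral t calculation gives 0.880.

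**4. Effect of dropping.** The share m without a baseline is an assumption, 5% to 10%, with no replacement. Then n = 42(1 − m).
- m = 5%: n = 39.9, power 0.875.
- m = 10%: n = 37.8, power 0.854.

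**5. Effect of keeping.** The correlation ρ between baseline and one post-baseline measure is also an assumption, 0.3 to 0.7. The SD is taken as the residual SD after baseline adjustment. A participant without a baseline then carries a fraction (1 − ρ²) of a complete participant's information, so n_eff = 42(1 − mρ²).
- m = 5%: n_eff 41.8 (ρ = 0.3) to 41.0 (ρ = 0.7), power 0.892 to 0.885. Gain over dropping: about 1 to 2 points.
- m = 10%: n_eff 41.6 to 39.9, power 0.890 to 0.875. Gain: about 2 to 4 points.

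In simulation (42 per arm, 4,000 runs), the complete-case variance was 1.04 to 1.07 times that of the joint model at 5% missing and 1.09 to 1.11 times at 10%. Neither was biased when baselines were missing completely at random.

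**6. Limit for plain mean substitution.** Step 5 assumes each participant is weighted by the information carried. Mean substitution with one common residual variance does not do this, and n_eff = 42 / [(1 − m) + m/(1 − ρ²)].
- ρ = 0.3: 41.8 and 41.6 at m = 5% and 10%, power 0.892 and 0.890. Same gain as step 5.
- ρ = 0.5: 41.3 and 40.7, power 0.888 and 0.882.
- ρ = 0.7: 40.1 and 38.3, power 0.877 and 0.859. Only 0.2 and 0.5 points above dropping.

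**The case against.** The strongest reply is that the inclusion rule follows from the endpoint. SAP section 4.6 defines the outcome as change from baseline, and protocol sections 4.7.2, 4.10.2.1 and 4.10.4 describe efficacy in the same terms. On that definition a participant without a baseline has no outcome. A reader might infer from the model specification that baseline is plainly just a covariate and the exclusion simply an error. The documents do not support that, because section 4.6 names both outcomes. The exclusion is avoidable only once total log CFU is confirmed as the dependent variable.

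Second, the sentence about using all results follows a replacement rule and may mean only that being replaced does not remove a participant's data. It is one sentence used twice, not two independent rules. It still conflicts with section 4.6 for someone without a baseline.

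Third, optional replacement (SAP sections 1.2 and 3.3; protocol section 4.7.1.1 for mothers) may restore numbers, so power need not fall as in step 4. This stands. It does not recover the excluded swabs.

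Fourth, baseline swabs are taken in hospital before any antiseptic, so few may be missing. This also stands; no rate is documented. Requiring a baseline and one follow-up value is moreover a common modified intention-to-treat convention. It is defensible if labelled as such.

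**Conclusion.** The inconsistency is real and minor. The primary population is described as everyone randomised, the model admits fewer, and the statement that all results are used is not met for participants without a baseline total.

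A reader might infer that the treatment comparison is biased. The documents do not show this: if baselines are missing completely at random, dropping these participants costs precision only. A reader might also infer a material loss of power. That cannot be derived from the documents either. With 5% to 10% of baselines missing, no replacement and a correlation of 0.3 to 0.7, keeping these participants could recover about 1 to 4 points for 0.82 SD between antiseptics at alpha 0.012. With plain mean substitution the gain shrinks to a fraction of a point at the top of that correlation range.

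The larger loss may come from mothers who deliver, or neonates discharged, before the first post-baseline swab. This point does not address that loss.

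**What to change.** In SAP section 4.6:

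1. Confirm total log CFU as the dependent variable, with baseline total as a covariate, and reconcile the bullet that names change.
2. Replace the inclusion bullet: the primary model includes all randomised participants with at least one post-baseline result, analysed as allocated.
3. State that a missing baseline covariate is replaced by the mean of observed baselines across all arms within the stratum (maternal or neonatal).
4. Describe this population accurately instead of as all randomised participants, and align SAP sections 1.2 and 3.3 with it.
5. Report by arm how many randomised participants have no post-baseline result.

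Fitting baseline as an outcome with a mean common to all arms is an alternative. It weights the retained participants properly and so keeps the gain at higher correlations, but it is a different model from the one specified, which allows a non-linear baseline term and a possible baseline-by-time interaction.

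The cost is wording plus one data step for mean substitution. No new data or recruitment is needed. Baseline adjustment is weaker for the few participants with a filled-in value.

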**Interaction analysis**

- Interactions between antiseptic and frequency, antiseptic and timepoint of swab, and frequency and timepoint of swabs will also be fitted in separate models, to assess evidence for the presence of interactions.
- Models and reporting of results will be as per the primary analysis.

**Repeated samples efficacy sensitivity analysis**

- Change from baseline to the:
  - first outcome measure after baseline
  - final outcome measure
 will also be modelled
- Model and reporting of results will be as the primary analysis except individual will not be fitted as a random effect (as there will be no repeated measures within individuals)

**Time since antiseptic efficacy sensitivity analysis**

- The primary analysis described above will be repeated with time since last antiseptic application fitted as a fixed effect (continuous; mfp will be used to assess linearity)

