### **Maternal participants in single application arms:**

Antiseptic: The antiseptic will be applied once to the vagina and perineum (more details [Section 4.6.2.1](#)) after the 1st assessment and swab. Following this, routine care at vaginal examination's will continue. Any antiseptic that is applied as part of routine care will be recorded on the CRF.

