## 1. Trial design

### 1.1. Design & outline

NeoVT-AMR is a randomised controlled factorial trial with 3x2 + standard of care (SOC) design with two independent strata – labouring mothers and hospitalised neonates. Within each stratum, 147 individuals will be recruited – 21 per treatment combination or SOC. Additionally, 147 babies from mothers in the maternal stratum will also be swabbed at birth.

The two factors are:

- Antiseptic: 1% chlorhexidine (CHG), 2% CHG and octenisept (OCT)
- Frequency of application: once only and multiple applications

Multiple applications timings are 0/4/8/24/28/32h in maternal strata and 0/1/2/3d in neonatal strata.

The SOC group will receive standard of care. For analyses, the reference arm will be 1% CHG once only as there are more effective replicates of each of the factorial arms and therefore greater power for comparison than with SOC. 1% CHG once only was selected as it would be the most straightforward to implement and CHG is more widely available than OCT so evidence of superiority of OCT over CHG would have to be shown for implementation to be advised.

The trial design is summarised in the trial scheme below. Note that the ‘once only’ frequency boxes are (n=21) also.

[figure not shown]

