#### **Neonatal strata**

- Change in neonatal skin bacterial load (in colony forming units)

Bacterial load will be assessed from vaginal and perineal swabs taken separately in the maternal strata and from neck and perirectal swabs taken separately in the neonatal strata. The log CFU for each swab will be summed to get the total log CFU. Timings of the swabs are the same as the timings for applications in the multiple application arm. Swabs are taken before antiseptic is applied.

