## **2.4. Sample Size Calculation**

There is very little data on bacterial load in neonates in LMICs. Additionally, bacterial loads are expected to differ across locations complicating interpretation of previous studies. For example, previous studies in neonates have found varying effects of CHG on log colony counts: a decrease from baseline to 24h of 0.2 SD with 1% CHG in Nepal (2) and 2SDs with 2% CHG in the USA (3). The primary endpoints of log colony forming units (CFUs) are widely accepted to be normally distributed. Sample size calculations used standard formula with Bonferroni adjustment for multiple testing within arms of frequency and antiseptic. Within each stratum, 147 individuals randomized to 7 treatment groups, 21 participants per group, provides 90% power to detect a difference of 0.82 standard deviations (SDs) between antiseptics (two-sided  $\alpha=0.012$ ) and 0.58 SDs between frequencies ( $\alpha=0.05$ ) (80% power for 0.72 and 0.50 SDs, respectively). This also provides 90% power to detect a difference of 1.01 SD between each antiseptic and SOC ( $\alpha=0.012$ ), and 0.90 SD between frequency and SOC ( $\alpha=0.025$ ) (0.88 and 0.79 SDs at 80% power). These expected effects were judged by clinical and statistical members of the team to be sufficient for selecting a treatment regimen for a future trial.

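### The time-since-antiseptic sensitivity model adjusts frequency for a covariate that frequency and swab hour fix, so its frequency coefficient is not a robustness check of the frequency effect

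*Protocol*

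**What the plan says.** The primary model in SAP section 4.6 is a mixed model with antiseptic, frequency, swab time and baseline load as fixed effects. Two of these matter here: "Frequency of application (once, multiple") and "Time point of assessment: hour of swab (continuous; mfp will be used to assess linearity"). The section headed Time since antiseptic efficacy sensitivity analysis then states that "The primary analysis described above will be repeated with time since last antiseptic application fitted as a fixed effect", again as a continuous term with mfp. Nothing is removed from the model, and nothing is said about how the frequency coefficient should be read afterwards.

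The schedule is fixed elsewhere. SAP section 1.1: "Multiple applications timings are 0/4/8/24/28/32h in maternal strata and 0/1/2/3d in neonatal strata". SAP section 2.1: "Timings of the swabs are the same as the timings for applications in the multiple application arm. Swabs are taken before antiseptic is applied". For the single arms, Protocol section 4.7.1.1 says "The antiseptic will be applied once to the vagina and perineum", after the first swab. The neonatal single arms follow the same pattern (Protocol section 4.7.1.2).

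**The concern.** Frequency is one of the two randomised factors, and the trial hypothesis in the Protocol's executive summary is that more frequent application reduces load further. A main way for repeat application to do this is to keep the time since the last application short. That time is a post-randomisation variable set by the frequency arm. Adjusting for it while keeping frequency in the model changes the question from whether frequency has an effect to whether the schedules differ at equal recency.

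The analysis is titled an efficacy sensitivity analysis of the primary result, so the natural reading is to set its frequency coefficient beside the primary one. If repeat application works by topping up a waning effect, the adjusted coefficient will shrink for structural reasons. A real benefit could then be reported as not robust.

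**Working it through.** **1. The plan's own frequency contrast.** SAP section 2.4 has "147 individuals randomized to 7 treatment groups, 21 participants per group" and gives "0.58 SDs between frequencies" at 90% power, 0.50 SD at 80%. Each frequency level pools three agents: 3 × 21 = 63 per side.

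- 90%: (1.960 + 1.282) × √(2/63) = 0.578 SD
- 80%: (1.960 + 0.842) × √(2/63) = 0.499 SD

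Both figures are reproduced. The trial was sized on once versus multiple, without conditioning on recency.

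**2. Time since last application (s) implied by the schedule.** Swabs precede the application due at the same time.

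| Stratum | Swab hour t | s, once | s, multiple |
|---|---|---|---|
| Neonates | 24, 48, 72 | 24, 48, 72 | 24, 24, 24 |
| Mothers | 4, 8, 24, 28, 32 | 4, 8, 24, 28, 32 | 4, 4, 16, 4, 4 |

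In the single arms s = t. In the multiple arms s is a fixed function of t. Under adherence, s carries nothing beyond arm and swab hour.

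**3. What the coefficient means.** Let F = 1 for multiple, and write the model as b·F + f(t) + g(s). The fitted multiple-minus-once contrast at swab time t is

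b + g(s in multiple at t) − g(t).

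At the first post-baseline swab s is the same in both schedules, so the g terms cancel and the contrast is b. This holds for any f and g, including mfp transformations, in both strata. By then both schedules have had one application at 0 h, so the true contrast there is 0.

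In neonates with linear terms, s = t − F(t − 24). Adding s is the same as adding F × (t − 24), the frequency-by-time interaction, with b read at 24 h.

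**4. Expected coefficient without and with s.** Linear terms, complete follow-up, benefit expressed with its maximum set to 1. The effect shapes are assumptions.

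| Stratum and benefit by swab | Without s | With s | Kept |
|---|---|---|---|
| Neonates, build-up 0, 0.5, 1 | 0.500 | 0.000 | 0% |
| Neonates, step 0, 1, 1 | 0.667 | 0.167 | 25% |
| Mothers, proportional to the gap in s (0, 4, 8, 24, 28 h, divided by 28) | 0.457 | 0.000 | 0% |
| Mothers, growing with number of applications (0, 0.25, 0.5, 0.75, 1) | 0.500 | 0.136 | 27% |
| Mothers, step 0, 1, 1, 1, 1 | 0.800 | 0.593 | 74% |

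The neonatal step can be checked by hand. The once arm is flat at 0. A line through 0, 1, 1 has mean 0.667 and slope 0.5 per 24 h, so its value at 24 h is 0.667 − 0.5 = 0.167. The fitted contrasts at 24, 48 and 72 h are 0.167, 0.667 and 1.167, which average 0.667. The effect is still in the model, but not in b.

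**5. Attrition and functional form (assumed patterns).**

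- Neonates, step, with early discharge: 16–21% kept.
- Mothers, step, last swab at 4/8/24/28/32 h in 40/30/10/10/10%: 68–75% kept (within-person correlation 0 and 0.5).
- Mothers, step, last swab at 4/8/24 h in 50/45/5%: 0.355 falls to about 0 (correlation 0).
- With time and s both fitted as categories, b is exactly 0 for the patterns tested (neonates step; mothers step and cumulative).

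**6. Simulation.** REML mixed model, 63 versus 63, correlation 0.5, maximum benefit 0.87 SD, 60 replicates, so the percentages are rough. Entries are the mean coefficient and the share with p < 0.05.

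| Scenario | Without s | With s |
|---|---|---|
| Neonates, linear build-up | −0.44 (97%) | −0.02 (3%) |
| Neonates, step | −0.59 (100%) | −0.17 (18%) |
| Mothers, step, complete | −0.70 (100%) | −0.52 (100%) |
| Mothers, step, attrition | −0.41 (85%) | −0.30 (60%) |
| Mothers, cumulative, attrition | −0.18 (30%) | −0.08 (12%) |

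**The case against.** A reader might infer that this analysis erases any real frequency effect. The documents do not support that as a general statement. In mothers the multiple-arm recency is 16 h at the 24 h swab and 4 h otherwise, so b is a fitted value pooled over all swabs, and up to about three quarters of the effect can remain in it. Even in neonates a step effect leaves 16–25%. Whatever leaves b goes into the recency term of the same model. Missed or interrupted applications, which Protocol sections 4.6.2.5 and 4.6.2.6 allow for, would loosen the link between arm and recency.

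The consequence can also be disputed. The primary frequency estimate does not contain recency and is untouched. SAP section 4 says that significant/not-significant conclusions will not be drawn, and section 4.6 says that analyses beyond the primary one may not be presented. A frequency-by-time-point model and separate models for the first and final swab are already planned, and together they would expose an absent early contrast beside a later benefit. Recency does not depend on the agent allocated, so antiseptic contrasts stay interpretable. Whether schedules differ beyond recency is a legitimate mechanistic question.

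A reader might also infer that standard-of-care comparisons are lost. That is minor: the primary model lists only the three agents, and comparisons with standard of care are optional.

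All of this stands, and it limits the scope. It does not make b an estimate of the frequency effect in either stratum, and no passage warns against reading it as one.

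**Conclusion.** The point holds for the frequency coefficient of this one sensitivity model. Under the planned schedule that coefficient is the modelled contrast at a swab where the two schedules have not yet diverged, so it cannot test the robustness of the frequency effect. For neonates with linear terms, about 75–100% of a real effect leaves it. For mothers the loss is about 25% to 100%. The algebra rests only on the schedule and adherence to it. The percentages rest on assumed effect shapes, functional forms, attrition patterns and within-person correlation. The SAP says that loss to follow-up may be high but gives no rate. The primary analysis and the antiseptic comparisons are not invalidated, and the sensitivity analysis need not be deleted.

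**What to change.** In SAP section 4.6, under the time-since-antiseptic analysis:

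- State that its frequency coefficient will not be reported or read as a robustness check of the frequency effect.
- Restrict the model to the antiseptic arms, because recency is undefined under standard of care. Fit recency in place of the frequency term, and label the result an exploratory description of waning.
- Judge robustness of the frequency effect from the frequency-by-time-point model in the Interaction analysis of the same section. Report the multiple-versus-once difference at each swab after the second application: 48 and 72 h in neonates; 8, 24, 28 and 32 h in mothers.

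The cost is SAP wording and minor analysis work. No new data or participants are needed.
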